### Evaluation of the implementation process

In order to evaluate the implementation process and detect barriers and facilitators, we will perform a comprehensive process evaluation. The following implementation constructs will be evaluated, as recommended by Steckler and Linnan [48]: context, reach, dose delivered, dose received, fidelity, implementation and recruitment. Further, the constructs maintenance and acceptability following recommendations of Proctor et al. will be evaluated. A combination of quantitative and qualitative methods will be used. Various data on the implementation process will be collected: drafts of regional action plans, field notes of training sessions, transcriptions of monitoring meetings, project meetings and interviews with implementation leaders and involved healthcare professionals.

### Implementation outcomes

*Context* refers to the larger physical, social, and political environment that either directly or indirectly affects the intervention. To study contextual characteristics of each intervention region, we will use field notes of training sessions, transcriptions of monitoring meetings, project meetings and interviews with implementation leaders and involved healthcare professionals.

*Reach* concerns the degree to which the intended audience participates in the intervention. Reach of the implementation strategy will be reported as the composition of the intervention teams, the absolute number and the proportion of professionals that participated in the training, using the attendance list of the training sessions. Reach of the intervention will be reported as numbers, proportions and characteristics of patients that received the integrated palliative care intervention.

*Dose delivered* is measured as the extent to which core elements of palliative care have been carried out by participating healthcare professionals, using questionnaires before and after the training. This measure reflects the effect of the implementation strategy on the care practices of each professional.

*Dose received* is measured as the extent to which core elements of palliative care are being received by participating patients, using patient questionnaires and medical chart review on received core elements.

*Fidelity* refers to the extent to which a patient was treated in accordance with the regional action plan. Fidelity checklists for each participating intervention patient will be filled out by the involved healthcare professional.

*Implementation* is a composite score indicating the extent to which the intervention has been implemented by professionals and received by patients. To compare the integrated palliative care provision between the intervention and control regions, the implementation score of delivered and received core elements of integrated palliative care will be calculated using the calculation method following Fleuren et al. [43].

*Recruitment* refers to the way we have recruited hospital regions to become involved in the implementation and evaluation of integrated palliative care in COPD.

*Maintenance* is the extent to which core elements of integrated palliative care is embedded in the routine organizational practices and policies.

*Acceptability* is the perception among healthcare professionals, patients and informal caregivers that the integrated palliative care intervention is agreeable, palatable, or satisfactory. We will perform semi-structured interviews with involved healthcare professionals on their experiences with the intervention and suggestions for improvement. A purposeful sample of patients and informal caregivers will be interviewed about their experiences with and perceptions about the care received and the information discussed with their healthcare professionals. Evaluation questionnaires will inquire on experiences with the training and toolbox and suggestions for improvement among participating professionals. The data will be used to make adaptations to the training and toolbox.

### Barriers and facilitators to implementation

The Consolidated Framework For Implementation Research will be used to explore what determinants to implementation are across different contexts. This framework consists of 37 constructs in five major domains: intervention characteristics, outer setting, inner setting, characteristics of the individuals involved, and the process of implementation. We will use the constructs to develop topic lists for semi-structured interviews with involved professionals.

### Data monitoring and management

All quantitative data will be collected using the online data management system Castor edc. For the management of participants, a secured Access database will be used. In case of errors or essential missing data, the participant or the concerning hospital will be contacted. Of eligible non-consenting patients their year of birth, sex and reasons for non-participation will be collected. The qualitative data gathered via monitoring and project meetings and interviews will all be audio-recorded and transcribed verbatim. The transcripts will be pseudonymized. Also, field notes made during training sessions and contact with professionals of the regions will be written out in digital documents. All study data and meta-data will be stored on a secured place in the Leiden University Medical Center for 15 years.

### Analysis

#### Analysis of effect evaluation

Data cleaning and all analyses will be carried out using statistical software that supports multilevel mixed model analyses, such as IMB SPSS Statistics 25. Baseline characteristics of region and study population will be analyzed using descriptive statistics. Continuous variables will be reported as mean and standard deviation and categorical variables as frequency or percentage. The statistical analyses will be done by an intention-to-treat approach. All analysis will be considered significant if α < 0.05. We will analyze differences between the control and the intervention group for the primary and secondary outcomes on the patient, informal caregiver and professional level using multilevel mixed model analyses that will account for the clustered study design (i.e. patients and professionals nested within a region). We will check for eventual unbalances in baseline characteristics and adjust for these variables if needed.

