**Methods:**

An integrated palliative care intervention was developed based on existing guidelines, a literature review, and input from patient and professional organizations. To facilitate uptake of the intervention, a multifaceted implementation strategy was developed, comprising a toolbox, (communication) training, collaboration support, action planning and monitoring. Using a hybrid effectiveness-implementation type 2 design, this study aims to simultaneously evaluate the implementation process and effects on patient, informal caregiver and professional outcomes. In a cluster randomized controlled trial, eight hospital regions will be randomized to receive the integrated palliative care approach or to provide care as usual. Eligible patients are identified during hospitalization for an exacerbation using the Propal-COPD tool. The primary outcome is quality of life (FACIT-Pal) at 6 months. Secondary outcome measures include spiritual well-being, anxiety and depression, unplanned healthcare use, informal caregiver burden and healthcare professional’s self-efficacy to provide palliative care. The implementation process will be investigated by a comprehensive mixed-methods evaluation assessing the following implementation constructs: context, reach, dose delivered, dose received, fidelity, implementation level, recruitment, maintenance and acceptability. Furthermore, determinants to implementation will be investigated using the Consolidated Framework for Implementation Research.

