## Methods

### Design

We follow an effectiveness-implementation hybrid design type 2, as proposed by Curran et al. [14], which allows us to simultaneously test the implementation strategy and impact of the integrated palliative care intervention on health outcomes. To study effectiveness, a cluster randomized controlled trial will be performed in eight hospital regions in the Netherlands. Furthermore, the implementation process will be evaluated using mixed methods. Each hospital region will serve as a cluster. Randomization on this cluster level instead of one-to-one randomization was chosen to reduce contamination: it is likely that professionals exposed to the implementation strategy also would treat patients assigned to the control condition differently [15].

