### Randomization

Hospital regions will be randomly allocated by an independent statistician to the intervention or control condition, stratified by the number of COPD exacerbation hospital admissions per year.

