### Effect evaluation

An overview of the data collection process, detailing the timing of data collection and the outcome measures and instruments used, is provided in Table 2.

**Table 2 Tab2:** Data collection schedule and measurement instruments for patients, informal caregivers and healthcare professionals

	Measurement instrument				
**Patient**		**T0**	**T3**	**T6**	**R**
Baseline characteristics	Questionnaire on demographic characteristics and case report form on disease severity	x			
Quality of life (primary outcome)	Functional Assessment of Chronic Illness Therapy-Palliative care (FACIT-Pal) scale [35]	x	x	x	
Spiritual well-being	Functional Assessment of Chronic Illness Therapy - Spiritual Well-Being (FACIT-Sp-12) scale [36]	x	x	x	
Anxiety and depression	Hospital Anxiety and Depression Scale (HADS) [37]	x	x	x	
Disease-specific health-related quality of life	Clinical COPD Questionnaire (CCQ)	x	x	x	
Satisfaction with care	Single item question on satisfaction with provided care, self-rated on a numeric rating scale (NRS) from 0 to 10	x		x	
Unplanned healthcare use	Medical record assessment on number of ED visits (without admission), hospital admission (number and number of days), ICU admission (number and number of days), in the 12 months pre-enrollment up to 12 months after enrollment				x
Date and place of death, place of care in last week of life if applicable	Medical record assessment (and contact with general practitioner if needed)				x
Dose received	Questionnaire on received core elements, based on three validated questionnaires [38–40]	x		x	
	Medical record assessment on core elements				x
Experiences and acceptability	Semi-structured interviews		x^a^		
**Informal caregiver**		**T0**	**T3**	**T6**	
Baseline characteristics	Questionnaire on demographic characteristics	x			
Caregiver burden	Caregiver Reaction Assessment (CRA) scale [41]	x	x	x	
Satisfaction with care	Single item question on satisfaction with provided care to the patient, self-rated on a NRS from 0 to 10	x		x	
Experiences and acceptability	Semi-structured interviews		x^a^		
**Health care professional**		**iT0**	**iT3**	**iT12**	
Self-efficacy	End-of-life professional caregiver survey (EPCS) [42]	x	x	x	
Role identity	Developed five-item question on role identity based on MIDI questionnaire [43]	x	x	x	
Satisfaction with care	Single item question on satisfaction with provided palliative care to patients with COPD, self-rated on a 5-point Likert scale	x	x	x	

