### Sample size calculation

Our primary outcome measure is quality of life measured with the FACIT-Pal. The clinically relevant difference is suggested to be between 4 to 6% of a measure’s overall score for the Functional Assessment of Cancer Therapy (FACT) scores, including the FACIT-Pal [45]. A previous systematic review on palliative care interventions used the 5% midrange bound, which equals 9 points on the FACIT-Pal [46]. Assuming a standard deviation of 25 [47], at least 121 patients per group are required to obtain a power of 80% (two-sided t-test, alpha = 0.05). To adjust for the clustering at hospital level (a previous study found an ICC = 0.01 [32]) and to allow for an additional loss to follow up of 10% a total of 347 patients are needed (44 patients per region).

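### The only covariate rule is to look for baseline imbalance and then adjust; adjustment for baseline FACIT-Pal is not assured, at a cost in precision

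*Protocol article*

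**What the plan says.** All references are to the protocol article.

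- **Analysis of effect evaluation.** Outcomes are compared between groups "using multilevel mixed model analyses that will account for the clustered study design (i.e. patients and professionals nested within a region"). The only sentence on covariates is "We will check for eventual unbalances in baseline characteristics and adjust for these variables if needed". It gives no list of candidate variables, no definition of imbalance and no criterion for when adjustment is needed.
- **Abstract, Methods.** "The primary outcome is quality of life (FACIT-Pal) at 6 months".
- **Effect evaluation, Table 2.** FACIT-Pal is scheduled at T0, T3 and T6.
- **Randomization.** Regions are allocated "stratified by the number of COPD exacerbation hospital admissions per year". The analysis section does not mention this factor.
- **Sample size calculation.** The calculation rests on an unadjusted two-sided t-test and then allows for clustering and loss to follow-up. No correlation with baseline enters it.

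**The concern.** A rule that looks first and adjusts afterwards has two weaknesses. It selects on the wrong property: a strong predictor that happens to be balanced stays out, and a weak one that happens to differ comes in. It also leaves several possible primary models open until the data have been inspected.

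The design makes it likely that the rule will be used. Only eight regions are randomised. Local staff identify patients and obtain consent after the regions are allocated (Procedures), and these professionals cannot be blinded to allocation (Blinding). Both chance and recruitment differences between arms are therefore realistic.

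For a continuous quality-of-life score, the baseline value of that score would usually be expected to be among the best predictors. If its use is left to chance or to a later decision, the trial may give up precision that its own data would provide.

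**Working it through.** **Inputs from the article (Design; Sample size calculation).** Difference 9 points, SD 25, two-sided alpha 0.05, power 80%, 121 per group, ICC 0.01, 10% loss to follow-up, total 347, eight regions.

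**Assumptions, not in the article.** Four regions per arm; a correlation r between T0 and 6-month FACIT-Pal of 0.3 to 0.7; the same proportional variance reduction within and between regions.

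**1. Reproducing the planned total.**
- Per group: 2 × [25 × (1.96 + 0.842) / 9]² = 121.1, which agrees with 121.
- Cluster size before inflation: 242 / 8 ≈ 30. Design effect: 1 + 29 × 0.01 = 1.29.
- Total: 242 × 1.29 / 0.90 = 346.9, so 347. The stated figure reproduces, with no baseline adjustment in it.

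**2. Standard error without baseline.**
- Analysed: 347 × 0.9 ≈ 312, or m = 39 per region.
- Between-region variance: 0.01 × 625 = 6.25. Within-region variance: 0.99 × 625 = 618.75.
- SE = √[(4/8) × (6.25 + 618.75/39)] = √[0.5 × 22.115] = 3.33.

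**3. Standard error with baseline FACIT-Pal always in the model.** Multiply by √(1 − r²). Power is for 9 points, from a noncentral t distribution with noncentrality 9/SE. The 6 df are eight regions minus two arms. The 5 df column adds a one-df stratum term that explains no variance.

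| r (assumed) | SE | Reduction in SE | Power, 6 df | Power, 5 df |
|---|---|---|---|---|
| not adjusted | 3.33 | – | 62% | 59% |
| 0.3 | 3.17 | 5% | 66% | 63% |
| 0.5 | 2.88 | 13% | 74% | 71% |
| 0.7 | 2.37 | 29% | 88% | 85% |

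**4. What an imbalance-triggered rule does.** The article gives no trigger, so one was assumed: adjust for baseline only if a patient-level t-test of the baseline difference gives p < 0.05. Simulation used 8,000 trials per setting, 39 patients per region and cluster-level tests on 6 df. Baseline was adjusted for in about 9–10% of trials. At r = 0.5:

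| Rule | Empirical SE | Power | Type I error |
|---|---|---|---|
| Never adjust | 3.32 | 61% | 5.0% |
| Adjust if imbalanced | 3.13 | 63% | 4.5% |
| Always adjust | 2.86 | 74% | 4.9% |

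The triggered rule recovers 0.19 of a possible 0.46 points of SE, and 2 of 13 percentage points of power. Its type I error is not inflated: 4.5% here, and 3.7% at r = 0.7.

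**The case against.** The strongest reply is that the imbalance sentence may not govern FACIT-Pal at all. Table 2 lists baseline characteristics in a row separate from quality of life, and the Baseline measures section names demographic and disease-severity variables but not FACIT-Pal. A mixed model could use T0 as a repeated outcome or as a covariate, and a fuller protocol or analysis plan may say so. This stands as far as it goes: the article is silent on T0 FACIT-Pal and does not exclude it. A reader might infer that FACIT-Pal enters only if it looks imbalanced, or that the stratum has been dropped from the model; the text supports neither. The reply does not rescue the sentence itself, which is an affirmative rule and the only one given.

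A second reply is that the rule does no harm to error rates. For one covariate under one fixed trigger, the simulation bears this out. A reader might infer inflated type I error, but that has not been shown. Free choice among several covariates was not simulated, so there the concern is discretion, not a measured error rate. Analysis under recoded identifiers (Blinding) limits steering towards an arm but does not fix the model in advance.

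A third reply concerns size. The correlation is assumed, and the unadjusted comparator supposes that baseline is never used. The distance between the planned 80% and 62% is also not due to covariates: it comes from the larger analysed cluster size (39 against 30) and the t reference on 6 df, which are separate matters. All of this is right. Only the direction of the gain follows from the design.

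**Conclusion.** The point holds in a limited form. The stated rule selects covariates after the data are seen and by observed difference, and as written it does not assure adjustment for baseline FACIT-Pal. The consequences are lost precision and an undefined primary model.

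Under the assumptions above, always adjusting lowers the SE by 5%, 13% or 29% for r = 0.3, 0.5 or 0.7, and raises power for 9 points from 62% to 66%, 74% or 88% on 6 df. With a one-df, non-prognostic stratum term as well, power is 63%, 71% or 85%; at r = 0.3 that is barely above the unadjusted figure.

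A reader might infer that leaving the stratum out of the model is itself an error. The documents do not support that. With eight regions, a stratum term costs about one of six between-region degrees of freedom (62% to 59% power at unchanged SE) and gains precision only if it is prognostic. Its case is consistency with the randomisation. The number of strata is not given, and more than two levels would cost more.

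The sponsor should make this change, but nothing here invalidates the trial.

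**What to change.** Replace the imbalance sentence in Analysis of effect evaluation with:

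> *The primary model includes arm and baseline FACIT-Pal as fixed effects and a random intercept for region. Each secondary outcome measured at T0 is adjusted for its own T0 value. No covariate in the primary model is selected on observed imbalance; adjustment for imbalanced characteristics is a sensitivity analysis.*

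If the sponsor wants the analysis to mirror the randomisation, the admissions stratum can be added as a single low-df term. That choice should be made before the data are seen, with its degree-of-freedom cost accepted.

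The cost is a short change of wording. The T0 measurements are already in the schedule, and neither sample size nor conduct changes. If an unpublished analysis plan already fixes these terms, the article and the plan need only be brought into line.

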#### Analysis of process evaluation

All quantitative process data will be analyzed using descriptive statistics. We will examine the association between the implementation score and each effect outcome measure at patient level, using linear regression analysis. For this analysis, the dependent variable is the implementation score. Independent variables are patient outcomes at measurement point T6 or T12. Transcriptions of the semi-structured interviews, monitoring sessions and project meetings will be analyzed using inductively and deductively content analysis techniques supported by the qualitative analysis software Atlas.ti. Subsequently, triangulation of quantitative and qualitative results will take place.

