However, it is not yet clear how palliative care can be successfully integrated into COPD-care. At the moment, discussions on prognosis, goals of care and advance care planning rarely occur or only at a very late stage of the disease [9]. Neither are patients with COPD regularly referred to specialist palliative care [10]. As a consequence, patients with COPD are less likely to die at their preferred place of death, and symptoms remain undertreated [4, 11]. Previous research revealed three major barriers to palliative care provision in COPD [9, 12]. First, the unpredictable disease trajectory of COPD makes it difficult to determine when to start palliative care and discuss advance care planning. The second barrier is the lack of palliative care communication skills of professionals. The third barrier is related to a lack of care continuity and collaboration between healthcare professionals [12, 13].

In the COMPASSION (a central element in the provision of COPD-care [13] and acronym for COPD Palliative and Supportive care Implementation) study, we attempt to overcome these barriers towards the implementation of palliative care. In collaboration with patient and professional organizations, we developed an integrated palliative COPD care intervention that integrates existing scientific and practical knowledge. Moreover, to facilitate uptake of the intervention among healthcare professionals, a multifaceted implementation strategy was developed comprising a training, an online toolbox and support with planning and monitoring of implementation.

In this article, we will describe the aim, design and procedures of the COMPASSION study. Both the implementation process and clinical effectiveness of the integrated palliative care approach will be assessed. The COMPASSION study aims to:
investigate the effect of the implementation of integrated palliative care on patient, informal caregiver and healthcare professional outcomes;investigate the effect of the multifaceted implementation strategy on implementation outcomes and explore what barriers hamper the implementation of integrated palliative care in routine COPD-care;explore the relationship between implementation level and patient outcomes.

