Furthermore, all hospital regions – including those randomized to the control group – wanting to participate in this study had a particular interest in this topic and were eager to change their care practice. Hence, this might lead to smaller differences between the provided care in the intervention and control group, and may decrease chances of detecting actual intervention effect. We attempt to deal with this by measuring and comparing the implementation score of delivered and received core elements of integrated palliative care between intervention and control groups.

Finally, it is uncertain what proportion of patients will score positively on the Propal-COPD tool and thus will be eligible for inclusion, as we made an assumption based on the development study [16]. Although the Propal-COPD tool is considered to be the best choice because it showed high sensitivity, its robustness and its feasibility in clinical practice need further testing. Therefore, we are planning to perform external validation with the data derived from this study.

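### Aim 2 asks for the effect of the implementation strategy, but the process analysis is fixed as descriptive, so the delivery measures get no between-arm estimate that respects the eight regions

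*Protocol article*

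**What the plan says.** All references are to the protocol article.

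- **Background, aim 2:** the study is to "investigate the effect of the multifaceted implementation strategy on implementation outcomes" and to explore barriers.
- **Design:** the hybrid type 2 design "allows us to simultaneously test the implementation strategy and impact of the integrated palliative care intervention on health outcomes".
- **Implementation outcomes, dose delivered:** "This measure reflects the effect of the implementation strategy on the care practices of each professional".
- **Implementation outcomes, composite score:** the score is calculated for a stated purpose: "To compare the integrated palliative care provision between the intervention and control regions".
- **Discussion:** motivated control regions may narrow the difference in care between arms. The response is: "We attempt to deal with this by measuring and comparing the implementation score".
- **Analysis of process evaluation:** "All quantitative process data will be analyzed using descriptive statistics". The section then adds one linear regression relating the implementation score to patient outcomes, and qualitative content analysis with triangulation.
- **Analysis of effect evaluation:** the multilevel mixed model that accounts for nesting within regions is assigned to primary and secondary outcomes.

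**The concern.** An aim worded as an effect, in a cluster randomised trial, calls for a between-arm estimate with an interval that reflects the unit of randomisation. The process analysis rules this out by assigning description to *all* quantitative process data.

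What is at stake is the evidence on whether the strategy changed the care given. Each intervention region writes its own action plan and may fine-tune the intervention, so delivery is likely to differ by region as well as by arm. A table of percentages or means by arm does not show whether a difference exceeds ordinary variation between regions. The Discussion nevertheless leans on that comparison when it deals with a possible narrowing of the contrast.

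**Working it through.** The article gives no sample size, ICC or precision for any implementation outcome (its sample size section concerns FACIT-Pal only), so there is no figure of the plan's own to reproduce here. The check sets the sections side by side.

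**1. Which measures carry aim 2 as a contrast between arms?** The Abstract names nine constructs: context, reach, dose delivered, dose received, fidelity, implementation level, recruitment, maintenance and acceptability. Dose delivered is described as reflecting the strategy's effect, and the implementation score is explicitly to be compared between arms. Dose received is one of the two components of that score. Context is studied in intervention regions, training reach and fidelity are recorded for those exposed to the strategy, and recruitment describes how regions were enlisted. None of these calls for a between-arm model. The gap concerns three of nine constructs.

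**2. Does any stated model give the contrast?**

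| Stated analysis | Applies to | Region-adjusted contrast between arms? |
|---|---|---|
| Multilevel mixed model | Primary and secondary outcomes | Yes, but not stated for the three measures |
| Descriptive statistics | All quantitative process data | No |
| Linear regression | Implementation score with patient outcomes | No; an association, with no region term stated |

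Neither the Abstract nor the Secondary effect outcomes section names dose delivered, dose received or the implementation score as a secondary outcome.

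**3. Are the data collected in both arms?** Table 2 schedules patient-reported dose received at T0 and T6, with a record review, and professional-reported dose delivered at iT0, iT3 and iT12. Procedures sends the professional questionnaires to all eight regions, and follow-up questionnaires to tool-positive patients without restriction by arm. The contrast can be estimated without new data.

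**4. What precision could be expected?** This is an illustration only.

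- *Degrees of freedom.* Eight regions in two arms leave 8 − 2 = 6 at region level. The 97.5% t quantile is 2.45 against 1.96 for the normal, and 2.45 / 1.96 = 1.25, so the interval is about 25% wider from this alone.
- *Clustering, for dose received only (measured on patients).* The inputs are 44 patients per region enrolled, and 44 × 0.9 = 39.6, taken as 39, after the planned 10% loss. The formulas are design effect = 1 + (m − 1) × ICC and standard-error factor = square root of the design effect.
  - ICC 0.01, the protocol's value for its sample size: 1 + 38 × 0.01 = 1.38 to 1.43, factor 1.17 to 1.20.
  - ICC 0.05 (assumed): 2.90 to 3.15, factor 1.70 to 1.77.
  - ICC 0.20 (assumed): 8.60 to 9.60, factor 2.93 to 3.10.

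The ICC of dose received is not given, so the two higher values are assumptions. The calculation does not carry over to dose delivered or to the composite score, because the number of professionals per region is not stated.

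**The case against.** **The Design wording describes a class of design.** The same section divides the work into a cluster trial for effectiveness and a mixed-methods evaluation of implementation. This softens the word *test*, and it means that the process evaluation is not empty: content analysis and triangulation are planned. It does not remove the explicit comparison of regions under Implementation outcomes, or the reliance on it in the Discussion.

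**The comparison is stated and only its model is missing, which a condensed article may leave to a fuller document.** This would succeed if the article were silent. It is not: it assigns description to all quantitative process data. A later plan that added a model would depart from that sentence rather than complete it.

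**The list of secondary outcomes is not closed.** This is fair: the Abstract names anxiety and depression as secondary and the later section omits them. Table 2, which includes the dose measures, also sits under Effect evaluation. Even so, the article defines these measures as implementation constructs and never names them as secondary effect outcomes.

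**With eight regions, description by region is defensible.** It is, if the aim is worded to match. It does not deliver an effect.

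A reader might infer more than the text supports:

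- *That false-positive rates are inflated.* No unadjusted significance test between arms is planned, so such rates would size an error that the plan does not make.
- *That the score contrast will be used to tell non-implementation from ineffectiveness if the primary result is null.* The Discussion says only that the score will be measured and compared because the contrast may shrink. It gives no rule tied to a null result.
- *That no process measure is modelled at all.* The regression for aim 3 is a model. It just does not compare arms.

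**Conclusion.** The point holds as a conflict within the article. Aim 2, Design, Implementation outcomes and Discussion call for a comparison of arms, while the process analysis prescribes description and one regression that answers another question. Followed as written, dose delivered, dose received and the implementation score have no between-arm difference or interval that respects the eight randomised regions.

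Its size is one of three aims and three of nine constructs. The primary outcome, its sample size and the secondary effect outcomes are untouched. The conclusion rests on reading *all* literally and on the three measures not being secondary outcomes. It does not depend on any assumed ICC. It should be corrected, at low cost, and does not threaten the trial's main result.

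**What to change.** In Analysis of process evaluation, limit the descriptive sentence to the remaining process data and add:

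*Dose delivered, dose received and the implementation score will be compared between arms with a multilevel model with region as random effect, the baseline value (iT0 or T0) as covariate where collected, and a small-sample degrees-of-freedom correction. The difference and its 95% confidence interval will be reported as a secondary estimate. Context, training reach, recruitment and fidelity will be described.*

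Three details need settling with it:

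- The small-sample correction must be written out, because Analysis of effect evaluation does not state one.
- For professionals, use the scheduled iT0, iT3 and iT12 questionnaires. Dose delivered is defined by questionnaires before and after training, but control regions are offered training only once recruitment has ended. Procedures times follow-up from training in intervention regions and from first patient inclusion in control regions, which should be acknowledged as a limit on comparability. The note to Table 2 times iT3 from first patient inclusion without distinguishing arms, so the two should be reconciled.
- State at which level (patient, professional or region) the composite score is calculated, since it combines delivery and receipt.

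The cost is a few models and no new data. The downside is wide intervals with eight regions, so the strategy's effect may look less certain than a table would suggest. If the investigators prefer description only, the alternative is to reword aim 2 and the Design statement as descriptive, and to present the comparison in Implementation outcomes and Discussion in the same terms.
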